### Selection criteria

Cases with a diagnosis of adenocarcinoma.Cases in which laparoscopic ileocecal resection, laparoscopic right hemicolectomy, or laparoscopic extended right hemicolectomy with D2 or D3 dissection are planned for clinical stage 0, I, II, or III colon cancer in the caecum, ascending, or transverse colon.Robot-assisted surgical cases will be eligible for inclusion only after the participating institution has demonstrated procedural proficiency through completion of at least 10 prior cases of ileocecal resection, right hemicolectomy, or extended right hemicolectomy for right-sided colon cancer.

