### Endpoints

The primary endpoint is the incidence of postoperative complications (Clavien–Dindo classification grade ≥ III) [35]. The rate of severe postoperative complications in all eligible patients will be investigated, and risk factors affecting them will be determined.

A key secondary endpoint is the incidence of intraoperative vascular injury around the SMV. The rate of intraoperative vascular injury around the surgical trunk in all eligible patients will be investigated, and risk factors affecting it will be extracted.

Other secondary endpoints include the incidence of postoperative complications (Clavien–Dindo classification grade ≥ II), 5-year overall survival, recurrence-free survival, and other short- and long-term outcomes (operative time, blood loss, conversion rate, degree of lymph node dissection, intraoperative complication rate, reoperation rate, R0 resection rate, local recurrence rate in the whole cohort and by stage, and incidence of bowel obstruction and herniated abdominal wall scarring). Factors influencing the above endpoints will be determined for all eligible patients. Furthermore, comparisons will be made between each subgroup, as shown in Table 1.

**Table 1 Tab1:** Secondary endpoints

1. Short-term results by approach (a. Medial approach vs. retroperitoneal approach; b. Medial approach vs. cranial approach; c. Retroperitoneal approach vs. cranial approach; a–c for laparoscopic surgery and robotic surgery, respectively)
2. Short-term results of robot-assisted and laparoscopic surgery (Comparison in all approaches, medial approach, retroperitoneal approach, and in each ASA-PS, respectively)
3. Short-term results by degree of lymph node dissection (D2, D3v, D3a)
4. Long-term results by approach, robot or laparoscopy, and degree of dissection
5. Impact of experience on short-term and long-term outcomes after the surgery performed by the surgeons before obtaining board certification in gastrointestinal surgery (including the investigation by each approach, robot/laparoscopy, and degree of lymph node dissection)
6. Impact of surgeons’ case volume prior to obtaining board certification in gastrointestinal surgery on short- and long-term outcomes following robot-assisted procedures
7. Impact of the participation of Endoscopic Surgical Skill Qualification-certified surgeons in surgery and their role in the procedure on short- and long-term outcomes
8. Impact of anastomosis method on short- and long-term outcomes

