Participating institution backgroundInstitution type and sizePatient backgroundPatient age; sex; body mass index; American Society of Anesthesiologists Physical Status; Eastern Cooperative Oncology Group performance status; albumin level; lymphocyte count; presence of dementia, diabetes, chronic kidney disease, chronic liver disease, or respiratory comorbidities; history of cardiac or cerebrovascular disease; use of steroids/immunomodulators and antithrombotic drugs; preoperative bowel obstruction; preoperative anaemia; abscess or peritonitis; preoperative therapy; history of laparotomy; timing of surgery; primary tumour location; and tumour stage at initial diagnosis (clinical stage, T factor, N factor).Technique and surgeonsWhether the surgeon is a board-certified gastrointestinal surgeon, whether an Endoscopic Surgical Skill Qualification-certified surgeon participates in the operation and his or her role, the approach, blood vessels to be dissected, procedure of dissecting the accessory right colic vein (via the cranial or caudal side), level and direction of lymph node dissection, instruments used during node dissection, method of anastomosis, combined resection of other organs, whether a robot is used, number of previous robotic-assisted right-sided colon resections (ileal resection, right hemicolectomy, or extended right hemicolectomy), and whether a robotic surgery proctor participates in the surgery if robotic surgery is used.Surgical outcomesThe date of surgery, operation time, blood loss, presence of intraoperative vascular injury, other intraoperative complications, 30-day postoperative survival, open conversion, intraoperative blood transfusion, details and grade of postoperative complications within 30 days (Clavien–Dindo classification grade ≥ II), onset and date of intervention for cases with anastomotic leakage/deep wound infection (surgical site infection [SSI]), enforcement and date of reoperation, drain placement, anti-adhesive placement, date of discharge, and operative death.In cases of intraoperative vascular injury:Timing of intraoperative vascular injury; response to intraoperative vascular injury; unplanned bowel resection due to bleeding; open conversion due to bleeding; final post-haemostatic status; and amount of blood transfusion, blood products, and albumin administered from intraoperative to postoperative day 3.Surgical deathsCause of death, date of death, and date of therapeutic intervention.Pathological and histological findings and postoperative courseTumour diameter, histological type (main), pathological stage, T-factor, N-factor, R-status, number of harvested lymph nodes, number of lymph node metastases, presence and details of adjuvant therapy, survival outcome, date of confirmation of final survival outcome, date of confirmation of recurrence, and type of initial recurrence.Patients with pStage 0 and pStage IV will be censored, and no follow-up will be performed after initial postoperative discharge. The development of intestinal obstruction (Clavien–Dindo classification grade ≥ II) and abdominal wall scar hernia will be investigated during follow-up. Patients will be followed up during the postoperative period according to the Japanese Society for Cancer of the Colon and Rectum guideline schedule, and tumour marker levels, thoracoabdominal computed tomography (CT) results, and colonoscopy results will be collected. Omitting observations as part of routine medical care will be deemed acceptable at the discretion of the treating physician [36].

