(15) Robot usage: classified into da Vinci (except SP), Hinotori, Hugo, other models, or no usage.(16) Anastomosis method: classified into functional end-to-end anastomosis, overlapping anastomosis, delta anastomosis, and others. Additionally classified as intracorporeal or via a small laparotomy.(17) Methods for dissecting the right accessory colonic vein: dissection from the cranial and caudal sides.(18) Direction of lymph node dissection: the dissection procedure of the surgical trunk is classified into caudal to cranial, cranial to caudal, and caudal to cranial after setting a cranial termination point.(19) Lymph node dissection: classified as D0–1, D2, D3v, and D3a. The definitions are as follows.aFor the ileocecal and right colic arteryD2, the ileocecal or right colic artery is dissected proximally without SMV exposure; D3v, the anterior face of the SMV is exposed, and the ileocecal or right colic artery is dissected proximally; D3a, the anterior face of the SMA is additionally exposed, and the ileocecal or right colic artery is dissected at the root.bFor the middle colic arteryD2, the right/left branch of the middle colic artery (MCA) is dissected proximally. The main trunk of the MCA is not exposed; D3v, the main trunk of the MCA and anterior face of the SMV are exposed, and the right branch or trunk of the MCA is dissected proximally; D3a, the MCA main trunk and anterior face of the SMA are exposed, and the right branch or trunk of the MCA is dissected at the root.

The degree of dissection is judged based on the dissection of the dominant main vessel, regardless of SMV exposure during the procedure.

(20) Synchronous other-organ resection: description of synchronously resected organs: duodenum, jejunoileum, colon, liver, gallbladder, pancreas, iliopsoas muscle, inferior vena cava, aorta, iliac artery and vein, SMA and SMV, peritoneum of the abdominal wall adjacent to the colon, gonadal vessels, mesentery of other intestinal tracts, and others.(21) Devices used during lymph node dissection: monopolar, bipolar (including sealing devices), ultrasonic coagulation, and incision devices.(22) Intraoperative vascular injury: intraoperative injury to any of the following vascular organs: SMA, SMV, accessory right colonic vein, ileocecal artery, right colonic artery, MCA, anterior superior pancreaticoduodenal vein, right gastroduodenal vein, gastrocolic trunk, terminal ileal branch, first jejunal vein, and others (e.g., inferior vena cava).

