(23) Final bleeding control: possible/impossible (operative death).(24) Timing of intraoperative vascular injury: during lymph node dissection, mobilisation, intracorporeal anastomosis, extracorporeal anastomosis, and others (described at the time of adhesion dissection, drain insertion, etc.).(25) Other intraoperative complications: list those requiring intraoperative intervention (e.g., injury to other organs).(26) Open conversion: a skin incision ≥ 8 cm is generally defined as an open conversion. However, if the incision exceeds 8 cm solely for the purpose of tumor extraction, it shall not be considered an open conversion.(27) Postoperative complications (within 30 days): Clavien–Dindo classification grade ≥ II should be used.(28) Date of onset of anastomotic leakage/deep SSI: the date of onset is defined as the earliest time of abnormality during the initial physical examination, such as fever, abdominal pain, abnormal discharge from the drainage tube, blood test, and imaging.(29) Treatment intervention date: the date of treatment intervention is defined as the date corresponding to any of the following: administration of medical therapy (in the case of Clavien–Dindo classification grade II); performance of endoscopic, surgical, or interventional radiology (IVR) procedures without general anesthesia (grade IIIa); performance of endoscopic, surgical, or IVR procedures with general anesthesia (grade IIIb); or admission to the intensive care unit (ICU) (grade IV). Additionally, in cases of anastomotic leakage or deep surgical site infection (SSI), the date should be recorded if a new percutaneous drain is inserted or an existing one is replaced.(30) 30-day death: death from any cause within 30 days of surgery.(31) Surgical death: 30-day death or death during hospitalisation 31–90 days postoperatively.(32) Histological type, pathological stage, T and N stages, and R status: according to the Japanese Classification of Colorectal, Appendiceal, and Anal Carcinoma, third English Edition [37].(33) Postoperative adjuvant therapy: indicate whether at least one course has been completed, and specify the type of chemotherapy administered.(34) Recurrence-free survival: duration from the date of first treatment (surgery or start of preoperative therapy) to the date of the last confirmed recurrence-free/recurrence.(35) Local recurrence: local recurrence will be assessed based solely on the initial recurrence, with distinctions made between lymph node recurrence, anastomotic site recurrence, and other locations.(36) Intestinal obstruction during follow-up (Clavien–Dindo classification grade ≥ II): only the first occurrence 30 days after surgery will be considered.(37) Abdominal wall scar hernia: this will be diagnosed based on imaging findings, such as CT, or palpation of the hernia in the surgical scar. Only the first occurrence 30 days after surgery will be considered.

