Secondary endpoints: Summary statistics for patient background and other surgical outcomes will be calculated. A multivariate logistic regression or multiple regression analysis will be performed using the factors listed in the survey items that may influence outcomes. A random-effects model will be used to account for differences between the centres. The main endpoint for short-term outcomes for each subgroup is postoperative complications (Clavien–Dindo classification grade ≥ II), and group comparisons will be conducted after propensity score matching (differences between groups will be tested using Student’s t-test and the χ^2^ test) and logistic regression to identify confounders. Multiple regression analysis will be used to analyse continuous variables. A random-effects model will be used to account for the differences between institutions. The Kaplan–Meier method will be used to plot cumulative late complication curves, local and overall recurrence-free survival curves, and overall survival curves for long-term outcomes. To account for confounding factors, a multivariate Cox regression analysis will be performed using preoperative and postoperative factors that may contribute to recurrence and late complications, and risk factors will be examined. In addition to regression analysis of factors, each factor will be discussed from clinical and medical perspectives to reach a combined perspective.

The number of experienced cases will be added to the factors in the multivariate analysis to examine their effect on the outcome. The correlation of the number of cases experienced and outcomes (operation time and blood loss) with the learning curve will be evaluated using the moving average method and the cumulative sum curve.

Statistical significance will be set at *p* < 0.05.

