## Discussion

Successfully performing surgical procedures without intra- or postoperative complications is critical. A national survey in Japan demonstrated that the mortality rate of right hemicolectomy was higher than that of low anterior resection [7]. However, no detailed studies regarding the factors influencing the safety of this procedure have been conducted. Therefore, we will conduct the SCaRLET study to identify the rate and cause of severe perioperative complications in laparoscopic right-sided colectomy.

To the best of our knowledge, this will be the first large prospective study of laparoscopic right-sided colectomy in Japan, with nearly equal numbers of laparoscopic and robotic procedures. This study is characterised by a low event selection bias owing to its prospective nature. It will be conducted at Japanese institutions that excel in JSLCS, with high proficiency levels of performing laparoscopic and robotic surgeries. Hence, the institutional experience will not affect the study outcomes, potentially determining the actual safety of the procedure. We will investigate the actual incidence and causes of high mortality rates due to the procedure, which have not yet been clarified. Furthermore, we will investigate the actual incidence and causes of intraoperative vascular injury, which may be the only critical aspect in D3 lymph node dissection.

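### Platform is coded by robot use and only open conversion is counted, which can bias the secondary robot-versus-laparoscopy comparisons, mainly on conversion rate

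*Protocol article*

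**What the plan says.** **Entry is by plan.** Selection criteria admit "Cases in which laparoscopic ileocecal resection, laparoscopic right hemicolectomy, or laparoscopic extended right hemicolectomy with D2 or D3 dissection are planned". Robot-assisted cases have an extra condition on the institution's prior experience, but the article shows no field for the planned platform.

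**Platform is by use.** The data list under Observation, investigation data, and methods collects "whether a robot is used, number of previous robotic-assisted right-sided colon resections". Item 15 of Definition of assessment data gives the answer options: "Robot usage: classified into da Vinci (except SP), Hinotori, Hugo, other models, or no usage". No option covers a robot that was planned and not used, or used for only part of the operation.

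**Conversion means open conversion.** Item 26 states that "a skin incision ≥ 8 cm is generally defined as an open conversion", with an exception for incisions enlarged only to extract the tumour. The data list likewise names only open conversion.

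**Both feed a planned comparison.** The secondary endpoints in Endpoints include "conversion rate, degree of lymph node dissection, intraoperative complication rate". Table 1 item 2 plans a comparison of "Short-term results of robot-assisted and laparoscopic surgery", and item 4 extends the platform comparison to long-term results. For subgroup comparisons, Statistical analysis says: "The main endpoint for short-term outcomes for each subgroup is postoperative complications" of Clavien–Dindo grade II or higher.

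**The concern.** Whether the robot was used is settled during the operation, after the plan has been made. Grouping by it selects on an intraoperative event. If a planned robotic case is given up before the robot is used, the stated categories place it with the laparoscopic cases, together with any complication or open conversion that follows.

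The conversion definition adds an asymmetry. A laparoscopic operation that cannot be completed has one exit, to open surgery, and that exit is counted. A robotic operation has a second exit, to laparoscopy, and that one is not.

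At stake is the reading of the robot-versus-laparoscopy results. The Background names that comparison as unresolved, and the Discussion promotes the study as one "with nearly equal numbers of laparoscopic and robotic procedures".

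**Working it through.** **1. The plan's own figure.** The article gives no number for platform assignment. Its one design figure is the target of about 2,000. With a 5% rate and ±1.0 point, the normal approximation gives 1.96² × 0.05 × 0.95 / 0.01² = 1,825. The exact binomial interval, with an average half-width of 1.0 point, needs about 1,940. The target is therefore reproduced. It concerns the whole cohort and does not depend on platform coding.

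**2. Where each case goes under the literal rules.**

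| Course of operation | Platform code | Complications fall to | Conversion counted? |
|---|---|---|---|
| Laparoscopy planned, opened | no usage | laparoscopy | yes, laparoscopy |
| Robot planned, never used, finished laparoscopically | no usage | laparoscopy | no |
| Robot planned, never used, opened | no usage | laparoscopy | yes, laparoscopy |
| Robot used, finished laparoscopically | robot model | robot | no |
| Robot used, opened | robot model | robot | yes, robot |

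Rows 2 and 3 change group. Row 4 stays in the robotic group and loses only the conversion event.

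**3. Effect on complications.** Inputs:
- N = 1,000 planned cases per platform, from the target of 2,000 and the expected near-equal split.
- The same true rate p on both platforms. The 5% is the article's planning rate for grade III or higher; 10% is an assumption standing in for a higher grade II or higher rate.
- A share f of planned robotic cases in which the robot is never used, and a risk ratio RR in those cases relative to p. Both are assumptions; the article gives neither.

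Robot rate = (pN − fN·p·RR) / (N − fN). Laparoscopy rate = (pN + fN·p·RR) / (N + fN).

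Example with p = 5%, f = 2%, RR = 3: 20 cases move and carry 20 × 0.15 = 3 events. Robot 47/980 = 4.80%, laparoscopy 53/1,020 = 5.20%, difference −0.4 points.

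| f | RR | Difference at p = 5% | Difference at p = 10% |
|---|---|---|---|
| any | 1 | 0.0 | 0.0 |
| 1% | 2 | −0.1 | −0.2 |
| 1% | 3 | −0.2 | −0.4 |
| 2% | 2 | −0.2 | −0.4 |
| 2% | 3 | −0.4 | −0.8 |
| 5% | 2 | −0.5 | −1.0 |
| 5% | 3 | −1.0 | −2.0 |

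The standard error of the difference is √(2p(1 − p)/1,000): 0.97 points at 5% and 1.34 points at 10%. With RR below 1 the sign reverses. At p = 5%, f = 2%, RR = 0.5, the rates are 49.5/980 = 5.05% and 50.5/1,020 = 4.95%, a difference of +0.1.

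**4. Effect on open conversion.** Assume a true open-conversion rate of 2.0% on each platform (20 per 1,000) and f = 2% (20 cases moved).
- If 10% of the moved cases are opened (2 events): robot 18/980 = 1.8%, laparoscopy 22/1,020 = 2.2%.
- If 25% are opened (5 events): robot 15/980 = 1.5%, laparoscopy 25/1,020 = 2.5%.
- If 2% are opened, the same as the rest: 2.0% on both.

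**5. Uncounted robot-to-laparoscopy conversions.** If a share c of 1,000 robotic cases is finished laparoscopically, 1,000c events are missing: 10 at c = 1%, 20 at c = 2%. Beside an assumed 2.0% open rate, c = 2% would mean 4.0% converted from the robot while 2.0% is reported.

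**The case against.** The strongest reply is that the article is condensed. The case report form may hold a planned-platform field, and by-plan versus as-used assignment could be settled in the full protocol or analysis plan. Item 15 sets no threshold for use, so the fate of an abandoned case is ambiguous rather than fixed, and nothing says that Table 1 item 2 must be grouped strictly as used. An as-used exposure is also a legitimate choice in an observational study. This limits how firmly the point can be put but does not remove it. The article prints a detailed list of 37 definitions, both platform entries are worded by use, and only open conversion is collected and defined.

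A reader might infer that failed robotic cases disappear from the robotic group. The text does not support that: once the robot has been used, the case keeps its robot code and its complications count against the robot.

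A reader might also infer that the coding makes the robot look safer. The documents give neither the share of abandoned cases nor their risk, so the direction is conditional. Large distortions need extreme inputs. If half of the abandoned cases were opened, 25 times the assumed 2% base rate, then at f = 2% the rates would be 10/980 = 1.0% against 30/1,020 = 2.9%. Nothing in the article supports such an input.

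Propensity matching and regression on laparotomy history, body mass index, obstruction, abscess or peritonitis and clinical T stage can absorb part of the preoperative risk behind abandonment. They cannot fully absorb what is found only once the operation has begun. Cases opened before lymph node dissection are excluded from the key secondary analysis, which limits any effect there.

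**Conclusion.** The point holds as a limited one. Under the stated rules, robot-to-laparoscopy conversions are not counted, and planned robotic cases in which the robot was never used can fall into the laparoscopic group. The comparisons affected are the secondary ones in Table 1 items 2 and 4, and the conversion rate is the outcome most exposed.

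For complications the effect is probably small. With abandonment of 2% or less and a risk ratio of 1 to 3, it is 0 to −0.4 points at a 5% rate and 0 to −0.8 points at a 10% rate, below one standard error (about 1.0 and 1.3 points). It favours the robot only if abandoned cases carry higher risk. These sizes rest on an assumed abandonment share, risk ratio and equal true rates.

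The whole-cohort incidences of grade III or higher complications and of vascular injury do not change with platform coding. Robot use as a factor in the regression models carries the same ambiguity as the group comparisons.

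**What to change.** - Record the planned platform for every patient and use it as the main grouping for the robot-versus-laparoscopy comparisons.
- Add two codes: robot planned but not used, and robot converted to laparoscopy.
- Report any conversion from the planned platform beside open conversion.
- Keep as-used grouping as a sensitivity analysis, and state what counts as use so that sites code alike.

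The cost is one extra field and two answer options. They can be back-filled from surgical schedules and operation notes before the short-term analysis, which starts no earlier than 120 days after enrolment closes. The sample size does not change. The robotic conversion figure may become less favourable.

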**Fig. 3 Fig3:**
[figure not shown]
Questionnaire regarding the preferred anastomosis for laparoscopic right colectomy. A nationwide questionnaire conducted in 2023 by the Japan Society of Laparoscopic Colorectal Surgery revealed institutional preferences for anastomosis techniques. (**a**) Extracorporeal anastomosis was predominant in conventional laparoscopic surgery, (**b**) while intracorporeal anastomosis was favoured in robot-assisted procedures

Given the above background, we have designed this prospective observational study to investigate factors influencing the safety of laparoscopic right-sided colon resection.

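### The open-conversion definition exempts long incisions made solely for tumour extraction but not those enlarged for extracorporeal anastomosis, so it can inflate the conversion rate in extracorporeal, mostly laparoscopic, cases

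*Protocol article*

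**What the plan says.** The rule is in the Protocol article, Definition of assessment data, item 26. It has two parts: "a skin incision ≥ 8 cm is generally defined as an open conversion", followed by the exemption "if the incision exceeds 8 cm solely for the purpose of tumor extraction, it shall not be considered an open conversion". It says nothing about an incision used for the anastomosis.

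Other places that bear on it:

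- Definition of assessment data, item 16, on the anastomosis: "Additionally classified as intracorporeal or via a small laparotomy". No length is given for the small laparotomy.
- Fig. 3 legend, on the 2023 survey of institutional preferences: "Extracorporeal anastomosis was predominant in conventional laparoscopic surgery", "while intracorporeal anastomosis was favoured in robot-assisted procedures". The percentages are not shown.
- Endpoints lists the conversion rate among the other secondary endpoints: "operative time, blood loss, conversion rate".
- Table 1, item 2, plans a comparison of "Short-term results of robot-assisted and laparoscopic surgery". Item 8 plans to study the "Impact of anastomosis method on short- and long-term outcomes".
- Statistical analysis makes grade II or higher complications the main short-term endpoint of the subgroup comparisons. From the key secondary analysis it excludes only conversions that occur before lymph node dissection.

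**The concern.** In an extracorporeal anastomosis the wound through which the specimen leaves also serves to join the bowel. If it is lengthened to 8 cm or more wholly or partly for that purpose, it is no longer *solely* for extraction, and the exemption fails on its wording. The case is then coded as an open conversion although the dissection was finished endoscopically. With an intracorporeal anastomosis this cannot happen.

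The outcome code therefore depends in part on anastomosis site. That is an exposure in its own right in Table 1 item 8, and by Fig. 3 it tracks the platform compared in item 2. What is at stake is a spurious difference in conversion rate, unfavourable to extracorporeal cases and, through them, to laparoscopy.

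There is also a mismatch at the boundary. The rule starts at 8 cm or more, while the exemption starts above 8 cm. An extraction-only incision of exactly 8 cm is caught by the first and not released by the second.

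**Working it through.** **Step 1: apply item 26 literally.** In each case the dissection was completed endoscopically and the wound is longer than 8 cm unless stated.

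| Purpose of the wound | Exempt? | Literal code |
|---|---|---|
| Extraction only, intracorporeal anastomosis | Yes | Not converted |
| Extraction only, exactly 8 cm | No (not above 8 cm) | Converted |
| Lengthened wholly or partly for extracorporeal anastomosis | No (not solely extraction) | Converted |

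The direction of any error follows from this table and the Fig. 3 legend, with no numerical assumption.

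**Step 2: is there a figure to reproduce?** No. The article states no conversion rate, no share of extracorporeal cases and no incision lengths. What follows is illustration only.

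**Step 3: model.** Observed rate = c + (1 − c) × e × q, where

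- c = true conversion rate, assumed 2% on both platforms;
- e = share with extracorporeal anastomosis, assumed 60/40, 80/20 or 90/10 (laparoscopic/robotic);
- q = share of extracorporeal cases with an incision of 8 cm or more made at least partly for the anastomosis, assumed 0 to 5% and the same on both platforms.

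Group size is 1,000 each, from the target of 2,000 (Target number of cases) and the nearly equal split expected in the Discussion.

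Worked example, e = 80/20 and q = 1%:

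- laparoscopic: 0.02 + 0.98 × 0.80 × 0.01 = 2.78%;
- robotic: 0.02 + 0.98 × 0.20 × 0.01 = 2.20%;
- difference: 0.98 × 0.60 × 0.01 = 0.59 points.

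The chance that a two-sided 5% test comes out significant against laparoscopy is Φ((d − 1.96 × SE0)/SE1), where d is the difference, SE0 the pooled and SE1 the unpooled standard error. Here that is Φ((0.00588 − 1.96 × 0.00697)/0.00697) = 13%. With no artefact it is 2.5%.

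| e (lap/robot) | q | Lap | Robot | Difference (points) | Chance significant against lap |
|---|---|---|---|---|---|
| any | 0 | 2.00% | 2.00% | 0 | 2.5% |
| 60/40 | 1% | 2.59% | 2.39% | 0.20 | 5% |
| 80/20 | 1% | 2.78% | 2.20% | 0.59 | 13% |
| 90/10 | 1% | 2.88% | 2.10% | 0.78 | 20% |
| 60/40 | 5% | 4.94% | 3.96% | 0.98 | 19% |
| 80/20 | 5% | 5.92% | 2.98% | 2.94 | 89% |
| 90/10 | 5% | 6.41% | 2.49% | 3.92 | 99% |

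**Step 4: extracorporeal against intracorporeal.** The spurious difference is (1 − c) × q: 0.98 × 1% = 0.98 points at q = 1%, and 0.98 × 5% = 4.9 points at q = 5%.

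**Step 5: can adjustment help?** At q = 5%, extracorporeal cases on either platform have an observed rate of 0.02 + 0.98 × 0.05 = 6.9%, and intracorporeal cases on either platform 2%. Within each stratum the platform difference is zero, so in this model adjusting for anastomosis site removes the artefact from Table 1 item 2. In item 8 anastomosis site is the exposure, so nothing is left to adjust for.

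**Step 6: after the fix.** If incisions for extraction and for extracorporeal anastomosis are both exempt, the artificial difference in this model is zero for every q.

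**The case against.** The strongest reply is that this is an ambiguity in wording and not a shown bias. Much of that stands.

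- *Generally* leaves sites room for judgement, so the literal code is not certain to be used. This does not settle the matter: across 73 facilities, discretion over an unaddressed case invites different coding.
- Item 16 speaks of a small laparotomy, so the protocol does not expect these wounds to reach 8 cm routinely. A wound that is long only because of the tumour is already exempt. The number of affected cases may be close to nil.
- Every input to the size is assumed. Fig. 3 reports institutional preferences, not case shares.
- Conversion is one of many other secondary endpoints.

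Four stronger readings are tempting, and the documents do not support them:

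- **That the rule does bias the platform comparison.** This needs a frequency of long anastomosis wounds that the article does not give.
- **That adjustment cannot help.** This is true only of Table 1 item 8. Anastomosis site is a recorded item and can be used in the robotic-laparoscopic comparison.
- **That the key secondary analysis is affected.** Its exclusion concerns conversion before lymph node dissection, and an anastomosis ordinarily comes later. Nor does item 26 say that abandoning the endoscopic approach through a wound under 8 cm is never a conversion.
- **That reasons for conversion other than bleeding go unrecorded.** This would rest on a condensed item list. The data-entry form is not shown.

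**Conclusion.** The gap in item 26 is real and its direction is fixed by the text. Read literally, it can raise the conversion rate in extracorporeal cases and hence in laparoscopic relative to robotic cases. The size cannot be determined. Under the assumed inputs, the spurious platform difference runs from zero to 3.9 points and the spurious extracorporeal-intracorporeal difference from zero to 4.9 points. Both ranges rest on a 2% true conversion rate and on q between 0 and 5%; the platform range also needs the assumed splits and the same q on both platforms. A negligible effect is compatible with everything in the article.

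The consequence stops at the conversion rate. The primary endpoint is not defined by it, and the main subgroup endpoint is grade II or higher complications. Severity: minor.

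**What to change.** Reword the exemption in item 26 along these lines: *an incision of 8 cm or more made solely for tumour extraction and/or extracorporeal anastomosis is not an open conversion.* This also brings the two 8 cm boundaries into line.

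Before the short-term analysis, ask sites to re-check only the cases already coded as converted. That is enough, because a wider exemption can only take cases out of the converted group.

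The cost is one sentence and a query that should concern few cases. The rate will be slightly less comparable with series that use a pure length rule; reporting the rate under the current wording alongside deals with that. Replacing the length rule altogether with one based on the purpose of the incision is a larger trade-off, since it asks for more judgement at each site, and this point does not require it.
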